total of the 9878 COVID-19 fatal cases in Belgium (between March 8th and June 2nd 2020) were reported from nursing homes (Sciensano, 2020). In May 2020, a pilot baseline seroprevalence study was conducted in NHs among Flanders, which showed that 24,5% and 19,1% of respectively NH residents and staff developed SARS-CoV-2 antigen-specific antibodies. Among the nine different nursing homes included in this study, a large variation in seroprevalence was seen ranging from 0,0% to 38,4% and 5,2% to 31,0% for residents and staff respectively (*unpublished data*). However, the degree of seroprevalence and sero-incidence for NHs in Brussels and Wallonia remains unknown. Furthermore, the pilot study conducted in May 2020 assessed the seroprevalence 4 to 6 weeks after the peak incidence of the first epidemic wave. Additionally, when a COVID-19 vaccination will be implemented, it will be of crucial importance to monitor the seroprevalence in Belgian nursing homes and assess the degree of persistence of this vaccine-induced immune response.

Therefore, our major study goals are to assess the current seroprevalence of SARS-CoV-2 in NH residents and staff in Belgium with subsequent 2-monthly follow-up of the sero-incidence over a period of 10 months. Furthermore, many questions remain unsolved about the proportion of asymptomatic cases of SARS-CoV-2 antibody positive NH residents and staff (and about their individual risk factors). Our secondary study goal is to gain additional insights on the association between seropositivity, clinical manifestation and COVID-19 disease outcome.

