### 2.4.1 Inclusion and exclusion criteria

NH residents and staff are considered for inclusion in the study. Both residents/staff that did experience COVID-19(-like) symptoms or had a positive COVID-19 test before, as well as residents/staff that did not experience COVID-19(-like) symptoms can participate in this study.

Participants can be included if they are  $\geq 18$  years old, have been informed (orally and by means of a written information form) on the goal of the study and the procedures of the study and have agreed to participate in the study by means of a signature on the informed consent form. In some cases, NH residents can give oral consent to their legal representative or caregiver, who will confirm this oral consent by their signature. Service flat residents are not considered as target population in this study and are therefore excluded. Temporary staff, employed for a period of less than 1 year starting from baseline collection, will also be excluded. Participants who are unable to provide a capillary blood sample for the point-of-care (POC) test will also be excluded.

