## **2.5 Sample size**

To assess the cumulative incidence after 10 months of follow-up in residential care centers in Belgium a sample of 381 participants (residents & staff) is required to estimate a proportion of 0.5 with a half-width of 5%, using a 95% Wilson score CI. As residents/staff are clustered within care facilities, the sample size will be augmented by the design effect. Assuming, 15 participants (7 residents and 8 staff) per institution after 10 months of follow-up, and an ICC of 0.12, the design effect is  $2.68 = (1 + 0.12 \times (15 - 1))$ . The total sample size required is  $1022 = 381 \times 2.68$ . At least 69 institutions, each including 15 participants, need to be included in this study, which brings the total sample size to 1035 after 10 months follow-up. In order to obtain at least 15 participants, in 69 institutions after 10 months of follow-up, assuming a drop-out rate of 0.2 and 0.4 for staff (changes in staff, sick leave and holidays) and residents (deceased, hospitalized or transferred residents), would require 22 sero-negative participants per care facility, (10 staff, 12 residents) in all 69 institutions. Assuming a seroprevalence rate of 0.5 at the baseline moment of the study would require 44 participants per care facility, (20 staff, 24 residents) in all 69 institutions.

A final sample size calculation will be performed to check whether the sample size obtained for the second research question will be sufficient for the analysis of the first research question.

To assess the seroprevalence in residential care centers in Belgium a sample of 381 participants (residents & staff) is required to estimate a seroprevalence of 0.5 with a half-width of 5%, using a 95% Wilson score CI.

As residents/staff are clustered within care facilities, the sample size will be augmented by the design effect. Based on the previous calculation, 44 participants (24 residents and 20 staff) will be sampled per institution. Assuming an ICC of 0.12, the design effect is  $6.16 = (1 + 0.12 \times (44 - 1))$ . The total sample size required is  $2347 = 381 \times 6.16$ . At least 54 institutions, each including 44 participants, need to be included in this study, which brings the total sample size to 2376 participants.

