For vaccinated NH residents only, a survival analysis will be performed to investigate the proportion of deaths within the study follow-up and the time (in days) to a confirmed COVID-19 death since 14 days after being fully vaccinated (full dose regimen). The survival or censoring time (in days) is registered since 14 days after being fully vaccinated until first event (or censoring moment). A non-COVID-19 related death will be considered as a competing risk in the analysis. If the proportional hazard assumption holds, a stratified (by NH) Cox proportional hazards regression model will be used to model the cause-specific hazards between seropositive and seronegative residents. The latter will be included as a time-varying covariate. A history of self-reported SARS-COV-2 infections, a time-varying NH vaccination degree, province, age, gender, care profile, and presence of COVID-specific comorbidities will be

considered for model adjustment.

7. To assess the duration of SARS-CoV-2 specific antibody response (seroreversion/no antibody response) since 14 days after being fully vaccinated among NH residents and staff in Belgium.

The duration of SARS-CoV-2 specific antibody responses among NH residents and staff in Belgium will be modelled by means of an interval-censored survival analysis. Seroreversion will be defined as a negative rapid test result after at least one positive rapid test result or as two succeeding negative test results (implying the participant did not seroconvert after vaccination within two to four months). The time interval to seroreversion/no response is the time interval between 14 days after the (second) vaccination date (full dose regimen) and the first test moment of a negative test result after at least one positive rapid test or of the two succeeding negative rapid test results. As a sensitivity analysis, the event will also be defined as two succeeding negative rapid test results (whether or not after at least one positive rapid test result), if the rapid test result would turn out to be unstable.

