If the proportional hazard assumption holds, a stratified (by NH) Cox proportional hazards regression model will be used to model the cause-specific hazards between vaccinated and

non-vaccinated residents, adjusting for history of self-reported SARS-COV-2 infections, and a time-varying NH vaccination degree. Propensity score methods will be applied to reduce the effects of confounding.

10. To assess the duration of SARS-CoV-2 specific antibody responses (seroreversion/no antibody response) since self-reported infection in a non-vaccinated residents/staff.

If sufficient non-vaccinated participants with self-reported infection would be available in the random selected sample, a survival analysis for interval censored data will be performed to investigate the time (in days) to a SARS-CoV-2 specific seroreversion/no antibody response since self-reported, natural SARS-CoV-2 infection. A participant is considered to have an event (seroreversion/no antibody response) during the interval between a positive and a negative rapid test result during the follow-up visits, or between the between the positive test date and the first visit date in case of a negative rapid test at the first test date. If the rapid test results would turn out to be unstable, a sensitivity analysis will be performed and an event is considered after two succeeding negative rapid test results during the follow-up study visits. The survival or censoring time will be expressed as an interval in days between the positive test date until the visit date with first event (or censoring moment). A Cox proportional hazards regression model for interval censored data will be used to model the hazard of a SARS-CoV-2 specific seroreversion/no antibody response since natural infection adjusted or stratified for staff and residents.

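### Objective 7 estimates antibody duration after vaccination without separating participants infected before vaccination from those with no known infection

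*Protocol*

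**What the plan says.** Objective 7 in Protocol section 3.2 (the fourth secondary objective in section 2.1) concerns how long antibody lasts after full vaccination in residents and staff. The duration "will be modelled by means of an interval-censored survival analysis". The clock starts 14 days after completion of the regimen. The event is a negative rapid test after a positive one, or two negatives in a row, the latter glossed as "implying the participant did not seroconvert after vaccination within two to four months". A sensitivity analysis covers unstable test results. The paragraph names no covariate, stratum or subgroup.

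Other parts of the Protocol bear on this:
- Section 1 says that, once vaccination starts, it will be crucial to "assess the degree of persistence of this vaccine-induced immune response".
- Section 2.4.1 admits people who "had a positive COVID-19 test before".
- Section 2.7.1 counts any IgM or IgG line as positive, whatever the source of the antibody.
- In section 3.2, objective 4 reports seroprevalence by self-reported infection history, objectives 5, 8 and 9 adjust for it, and objective 6 considers it for adjustment.
- Objective 10, the parallel analysis of antibody after natural infection, is confined to non-vaccinated participants and is "adjusted or stratified for staff and residents".

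**The concern.** The rapid test cannot tell antibody from infection from antibody from vaccination. A participant already seropositive from an earlier infection may test positive at every visit for reasons unrelated to the vaccine, and would then count as a lasting response. Such a person is also unlikely to produce the two negatives that objective 7 reads as failure to respond to the vaccine, so a true non-response could go unseen.

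The result is a mixture whose shape depends partly on how many participants were infected in earlier waves. In the pilot, resident seroprevalence by home ran from 0.0% to 38.4%, so the mixture also depends on which homes are sampled. The reader most likely to use the result is a public health authority asking how long protection lasts in residents who were never infected. The curve does not isolate that group. Objective 10 keeps infection-derived antibody apart from vaccination, but objective 7 does not do the reverse.

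**Working it through.** The Protocol gives no figure for objective 7, so there is none to reproduce. The check has two parts: what the paragraph fixes, and how far a mixture could mislead.

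**1. The text.** Of the six other analyses in section 3.2 that involve vaccination status or time since vaccination (objectives 4, 5, 6, 8, 9 and 10), five use infection history and the sixth restricts to the non-vaccinated. Objective 7 does neither. Objective 4 does not fill the gap, because it splits seroprevalence and not duration. The dried-blood-spot sub-study (Appendix 6.4) measures anti-S1 and anti-NCP antibody but is not linked to objective 7.

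**2. Size.** Let π be the share infected before vaccination, and let L be the proportion who lose or lack antibody by month 10.

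- Overall loss = π × L(previously infected) + (1 − π) × L(naive)
- Understatement of loss in the naive = L(naive) − overall loss = π × [L(naive) − L(previously infected)]

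Inputs:
- π = 19.1% (staff) and 24.5% (residents), from the May 2020 pilot in section 1.
- L = 10% in the previously infected and 40% in the naive. Both are illustrative; the Protocol gives neither.

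Results:
- π = 0.191: 0.191 × 10% + 0.809 × 40% = 34.3%. Understatement 0.191 × 30 = 5.7 points.
- π = 0.245: 0.245 × 10% + 0.755 × 40% = 32.7%. Understatement 0.245 × 30 = 7.4 points.

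**3. Sensitivity to the assumed rates.** With persistence P = 1 − L at day 300, the overstatement of persistence is π × [P(previously infected) − P(naive)]:

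| P naive | P previously infected | π = 0.191 | π = 0.245 |
|---|---|---|---|
| 50% | 50% | 0 | 0 |
| 50% | 70% | 3.8 | 4.9 |
| 70% | 95% | 4.8 | 6.1 |
| 50% | 90% | 7.6 | 9.8 |
| 30% | 90% | 11.5 | 14.7 |

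Entries are percentage points. By the same formula, the sign reverses if the previously infected lose antibody sooner.

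**The case against.** The strongest reply is that silence is not a rule. The paragraph does not say that the analysis is pooled or unadjusted, and covariates of a secondary model are often left to a separate analysis plan. A reader might infer that the Protocol commits to one unadjusted estimate, but that is an inference from the absence of any split. The reply has limits. The table of changes calls section 3 the statistical analysis plan, objective 7 defers nothing, and the neighbouring objectives do name their handling of infection history.

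A second reply is that objective 7 speaks of antibody specific to SARS-CoV-2, not of vaccine-induced antibody, so time spent seropositive after vaccination is a legitimate description of the whole cohort. That is fair, and the overall curve may be kept as such. But the background sets persistence of the vaccine-induced response as the aim, and objective 7 itself reads repeated negatives as a failure to respond to vaccination.

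Four stronger readings are not supported:
- **That previously infected people stay positive whatever the vaccine does.** Objective 10 models loss of antibody after natural infection, so the Protocol expects it to occur.
- **That the distortion is 15 points.** That figure (0.5 × 30) takes its share from section 2.5: "Assuming a seroprevalence rate of 0.5 at the baseline moment of the study". This is a planning value. The pre-vaccination figures observed in nursing homes are the pilot's.
- **That vaccine product must be a stratum.** No analysis in section 3.2 uses product, and the documents give no evidence that persistence differs by product.
- **That a rapid test before the first dose can define the naive group.** Vaccination began on 5 January 2021 and Table 1 marks the first sampling in February. In the first round only 15% of sampled staff were unvaccinated. Few participants will have such a test.

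**Conclusion.** The point holds in a limited form. As written, objective 7 gives an overall curve for previously infected and infection-naive participants together, and that curve cannot by itself show how long a vaccine response lasts. The conclusion rests on the text and on the other objectives' use of infection history.

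The direction and size of any distortion cannot be computed from the Protocol. If previously infected participants stay seropositive longer, persistence in the naive is overstated by about 6 to 7 points at the pilot seroprevalence, under the illustrative 10% and 40% rates. The bias is zero if the groups persist equally. The pilot covered nine Flemish homes in May 2020, so the share infected by the time of vaccination may differ. This point concerns infection before vaccination only. It affects a secondary objective and is worth correcting because the remedy is cheap.

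**What to change.** In objective 7, report duration separately for participants with and without a reported positive test dated before vaccination, using a rapid test taken before the first dose where one exists. Make the group without prior infection the main estimate of vaccine-response duration. Adjust or stratify for staff and residents, as objective 10 does. Vaccine product may be an optional covariate. The overall curve can stay as a description of the cohort.

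The baseline questionnaires already ask for the approximate date of the first positive test and the date of the first dose, so infection can be ordered against vaccination without new data.

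Costs:
- **Precision.** If the split matched the pilot shares, the main group would hold 75.5% to 80.9% of participants. With standard error proportional to 1/√n and clustering ignored, its interval widens by 1/√0.809 = 1.11 to 1/√0.755 = 1.15. The previously infected stratum widens by 1/√0.245 = 2.0 to 1/√0.191 = 2.3.
- **Misclassification.** Section 1 notes that mild and asymptomatic cases often went untested. Unrecognised infections will remain in the naive group, so the split reduces the mixing but does not remove it. The report should say so.

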| Secondary objectives                              | This study was designed late 2020, when COVID-19 vaccines were still in research development. However, on January 5 th , 2021, the vaccination campaign in Belgian NH started. The implementation of vaccines directly impacts the seroprevalence, meaning that some of the secondary objectives were no longer accurate (e.g., assessment of risk factors for infection). Therefore, adjustments were made to the secondary objectives, and tertiary objectives concerning the proportion in the sample that is not vaccinated were added. | 2.1 Objectives
3. Data analysis                                                                |
| Additional questions concerning vaccine hesitancy | In the first test round we observed that 15% of staff in the sample were not vaccinated against COVID-19. Therefore, we aim to explore the reason behind vaccine hesitancy by adding additional questions in the follow-up questionnaire of the following sampling point concerning if and why they hesitated/are hesitating to get vaccinated as a part of the follow-up questionnaire (one-off).                                                                                                                                                     | 2.7.2 Demographic and medical data
6.3 Appendix: questionnaires                                |
| Statistical analysis                              | The statistical analysis plan was adjusted to the changes made in the secondary objectives and addition of tertiary objectives.                                                                                                                                                                                                                                                                                                                                                                                                                        | 3. Data analysis                                                                                  |

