## **2.7 Data Collection**

### **2.7.1 Collection of capillary blood samples and point-of-care test procedures**

The capillary blood samples will be obtained using a lancet to finger prick the middle finger and collect a 1-10 drops of capillary blood. A capillary blood drop will be transferred to the

specimen well of a point-of-care (POC) test (COVID-19 IgG/IgM Rapid Test Cassette, Orient Gene Biotech Co.) using a plastic dropper (delivered with COVID-19 IgG/IgM Rapid Test kit). Two drops (ca. 80 µl) of Orient Gene Biotech sample buffer will be immediately added to the buffer well, with avoidance of air bubbles. If the red colour does not move across the test window or if blood is still present in the specimen well after two minutes, one additional drop of sample buffer should be added into the buffer well. The result should be read in 10 minutes, positive test results may be visible as soon as 2 minutes. The result cannot be interpreted after 15 minutes.

The results of the COVID-19 IgG/IgM Rapid Test Cassette should be interpreted as following:

- **Negative:** The coloured line in the control region (C) changes from blue to red. No line appears in the test line region M or G.
- **Anti-COVID-19 IgM positive:** The coloured line in the control region (C) changes from blue to red and a line appears in the test line M.
- **Anti-COVID-19 IgG positive:** The coloured line in the control region (C) changes from blue to red and a line appears in the test line G.
- **Anti-COVID-19 IgG and IgM positive:** The coloured line in the control region (C) changes from blue to red and a line appears in the test line G and M.
- **Invalid test:** Control line is still completely or partially blue and fails to completely change from blue to red. Insufficient specimen sample or incorrect procedural techniques are the most likely reasons for control line failure. The test should be repeated using a new cassette.

For the study any positive result of IgM or IgG will be considered as a positive result. In case of an invalid test, the test is repeated. When it is still invalid it will be noted as such. Additionally, a few drops of capillary blood will be collected on Dried Blood Spot (DBS) collection cards for (semi-)quantitative analysis of vaccine-induced/infection-induced anti-SARS-CoV-2- specific antibodies as a part of the sub-study performed by Ghent University (details are provided in appendix 6.4).

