### **4.3 Bias and limitations**

- Loss of follow-up or missing data is possible, for instance, when a NH staff-member is not present at the moment of sample collection or a sample was not collected due to heavy workload. In this case, effort will be made to contact the NH and collect the sample within two days after the sampling day. In case of, for instance hospitalization of NH resident or self-isolation of NH staff, missing test result data is inevitable. In order to prevent missing data in the online questionnaires, results will be monitored and effort will be made to remind participants to fill in the survey (by e-mail/telephonic contact or at the moment of testing).

- Underestimation of the presence of SARS-CoV-19 seroprevalence among this population due to:

- Testing method limitations, however, the COVID-19 IgG/IgM Rapid Test Cassette (Orient Gene Biotech Co.) provides good sensitivity (92,9%) and specificity (96,3%) (Sciensano, 2020).
- Data collection, however, researchers/CRC's in charge of collecting the samples will be trained to ensure correct use of the COVID-19 IgG/IgM Rapid Test Cassette and interpretation of the results to minimize reporting bias.

- Due to practical limitations, seroprevalence data cannot be collected at the same point in time in all participants in this study. Seroprevalence, however, is subjected to fluctuations of the infection rate in the current SARS-CoV-2 pandemic and is therefore also time-dependent. Therefore, the maximal difference between the first and last samples collected within the baseline collection round is set at  $\pm 4$  weeks days.

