#### **6.4.3. Study design**

This sub-study follows the same time scheduling as the seroprevalence study. For each participant, in addition to every POC rapid antibody test, a few drops of capillary blood will be collected on a Dry Blood Spot saver card (4 saturated spots).

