#### **6.4.4. Data collection and analysis**

Only biological specimens will be collected. No additional questionnaire will be needed. The collected dry blood spots will be send back to Ghent University and saved in a study-specific biobank. The collected samples will be analyzed using an Enzyme-Linked Immuno Sorbent Assay (ELISA) for (semi)-quantitative detection of anti-SARS-CoV-2 specific antibodies (anti-S1/anti-NCP). The Dry Blood Spot samples will be pseudonymized.

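### Objective 7 reads a negative rapid test as lost or absent vaccine antibody, but the protocol does not show how well that test detects vaccine-induced antibody, and no section 3.2 analysis uses the paired ELISA.

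*Protocol*

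**What the plan says.** Objective 7 in protocol section 3.2 (the fourth secondary objective in section 2.1) concerns the duration of the antibody response from 14 days after full vaccination, by interval-censored survival analysis. The event takes two forms. The first is given as "Seroreversion will be defined as a negative rapid test result after at least one positive rapid test result". The second is a pair of consecutive negatives, which the protocol takes to mean that there was no seroconversion within two to four months of vaccination. A sensitivity analysis counts only consecutive pairs of negatives, with or without an earlier positive. It is run only if the cassette proves unstable, and what counts as unstable is not defined.

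The rapid cassette gives a yes/no result. Section 2.7.1 says: "For the study any positive result of IgM or IgG will be considered as a positive result". Section 4.3 says that the cassette "provides good sensitivity (92,9%) and specificity (96,3%) (Sciensano, 2020"). It does not name the population in which these figures were obtained.

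The table of changes says: "This study was designed late 2020, when COVID-19 vaccines were still in research development". It dates the start of the nursing-home campaign to 5 January 2021 and explains that the secondary objectives were revised for that reason.

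Appendix 6.4 describes a second measurement. Section 6.4.3 says: "For each participant, in addition to every POC rapid antibody test, a few drops of capillary blood will be collected" on a dried-blood-spot card. Under section 6.4.4 these spots are analysed by ELISA "for (semi)-quantitative detection of anti-SARS-CoV-2 specific antibodies (anti-S1/anti-NCP"). No analysis in section 3.2 refers to these results.

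**The concern.** The objective is about antibody, while the event is about the line on a cassette. Treating the two as equal requires evidence that the cassette reliably detects antibody raised by vaccination. The protocol's only evidence comes from a source dated before the nursing-home campaign, and neither the validation population nor the cassette's target antigen is given.

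Two separate problems follow. First, a single missed line after an earlier positive is enough for an event, so ordinary random error accumulates over repeated visits. Interval censoring allows for not knowing the event date; it does not correct an event that never happened. Second, a participant whose antibody lies persistently below what the cassette can show is negative at every visit and is labelled a non-responder. Repeating the same test cannot reveal this.

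At stake is the interpretation of an objective that the background section calls crucial. Section 4.4 sends results to public health authorities after every testing point.

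**Working it through.** The protocol sets no target figure for objective 7. The sample size (69 homes x 44 = 3036) serves the primary objectives and is unaffected.

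**Inputs**
- Sensitivity per test: s = 0.929 (section 4.3), applied to vaccine antibody as a working assumption.
- Tests per participant: k = 6, at months 0, 2, 4, 6, 8 and 10 (section 2.4). This is a maximum, because drop-out and tests before full vaccination reduce it.
- The participant truly keeps antibody throughout, so every negative is a miss.

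**Main definition, independent errors.** An event is any negative after a positive, or two negatives in a row. Only two sequences avoid it: all positive, or one negative at the first test followed by all positives.

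P(no event) = s^k + (1 - s) x s^(k-1) = s^(k-1)

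P(false event) = 1 - s^(k-1)

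- k = 6: 1 - 0.929^5 = 1 - 0.692 = **30.8%**
- k = 4: 1 - 0.929^3 = 19.8%
- k = 3: 1 - 0.929^2 = 13.7%

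**Two succeeding negatives only, k = 6.** Write q = 0.071 and sum the sequences with no two adjacent negatives:

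- s^6 = 0.6428
- 6 x q x s^5 = 0.2948
- 10 x q^2 x s^4 = 0.0375
- 4 x q^3 x s^3 = 0.0011

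The total is 0.9763, so P(false event) = **2.4%**.

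**Other assumed sensitivities, k = 6, independent errors**

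| Sensitivity | Main definition | Two negatives |
|---|---|---|
| 0.80 | 67% | 16% |
| 0.90 | 41% | 4.6% |
| 0.929 | 30.8% | 2.4% |
| 0.95 | 22.6% | 1.2% |
| 0.99 | 4.9% | 0.05% |

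**Misses correlated within a person.** With a beta-binomial model, mean sensitivity 0.929 and an assumed correlation of 0.1 to 0.7, the main definition gives 26% to 12% and the two-negatives rule gives 4.6% to 7.7%. If every miss were fully persistent, both rules would give 1 - 0.929 = 7.1%. The fallback therefore protects against random misses and loses its advantage as misses become persistent.

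**What cannot be computed.** The protocol gives no cassette sensitivity for vaccine antibody and no ELISA cut-off or performance. No corrected duration or response rate can be derived.

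**The case against.** The strongest reply is that unknown performance is not demonstrated bias. That stands. A reader might infer that non-response will be overstated and duration understated because the cassette is weaker for vaccine antibody. The documents do not say it is weaker, and false positives (3.7% per test at 96.3% specificity) act the other way by delaying events.

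A reader might also attach a size to the bias. If 95% of vaccinees have antibody, apparent seroprevalence is 0.95 x s + 0.05 x 0.037: 88.4% at s = 0.929, 80.9% at 0.85, 71.4% at 0.75 and 61.9% at 0.65. The 95% and the three lower sensitivities are illustrative values with no basis in the protocol. Comparing this spread with the 5% half-width in section 2.5 would also mislead, since that target belongs to the primary objectives.

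Other points stand in part. The ELISA is not idle: it serves a sub-study in the same participants at the same visits. Section 4.3 already concedes underestimation of seroprevalence from test limitations, though not specifically for vaccine antibody. The ELISA's performance on dried blood spots is undocumented, so making it the sole defining assay now would replace a test with quoted figures by one with none. Section 4.1 names no ELISA cost, although section 6.4.4 says the samples will be analysed.

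One could also leave the matter to the SAP. But the protocol itself fixes the event and the inference from two negatives, and a SAP that follows it inherits both.

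**Conclusion.** The concern holds as a gap in evidence and interpretation, not as a proven bias of known direction. The protocol equates a negative cassette with lost or absent vaccine antibody without showing that the cassette's performance extends to vaccine-induced antibody. That the quoted figures predate vaccination is inferred from the 2020 citation and the January 2021 campaign start.

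The firmest figure concerns random error. At the quoted 92.9%, up to 30.8% of participants with no true loss would be coded as events under the main definition. This assumes six usable tests and independent errors; fewer tests or correlated errors lower it. The two-negatives rule brings it to 2.4% under the same assumptions, but it is run only if results prove unstable, and being based on the same cassette it cannot detect persistent misses. The primary objectives' sample size does not change.

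**What to change.** 1. In section 3.2, title the cassette analysis of objective 7 *time to rapid-test negativity*, and remove the inference that two negatives mean no seroconversion.
2. Link the anti-S1 ELISA results from appendix 6.4 to the rapid-test data by identification code. Report cassette agreement and sensitivity against the ELISA separately for vaccinated and previously infected participants. Add an ELISA-based analysis of objective 7 that is always run, with the cut-off fixed before analysis.
3. State in section 4.3 that the 92.9% and 96.3% figures are not shown to apply to vaccine-induced antibody.

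The cost is wording in sections 3.2 and 4.3 and the linkage of two datasets. No sampling or assays are needed beyond those already planned. The ELISA-based analysis must wait for the sub-study batches. The ELISA's performance on dried blood spots would have to be documented before it could replace the cassette as the main definition; until then it is a parallel analysis.
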